### Group allocation and blinding

Participants will be assigned using blocked stratified randomization with allocation concealment to one of two training groups: 1) perturbation training, or 2) ‘traditional’ balance training (control). To maintain allocation concealment, a variable block size ranging from 4–8 will be used. There will be four strata based on two stratification factors: site (two levels), and frequency of ‘failures’ during baseline reactive balance control assessment (two levels). Stratification by site will ensure that the treatment groups are balanced within each institution accounting for potential differences in intervention administration between sites. Balance recovery ‘failures’ are defined as use of the overhead support harness and/or research assistant to prevent a fall to the floor, or stepping with the blocked limb during the encouraged-use condition; high frequency of failure predicts falls in the community [27]. Frequency of failures will be classified as either ‘high’ (≥10 % of trials) or ‘low’ (<10 % of trials). This approach will help to ensure that the groups do not differ significantly on this prognostic factor [38, 39], particularly within each site, and that there will be approximately equal numbers of participants assigned to each group. Group allocation will be performed centrally by the principal investigator, who will not be involved in recruiting, assessments, or administering the interventions. The random allocation sequence will be computer generated and maintained in an electronic file by the principal investigator.

Each site will be staffed by two individuals: a research assistant and a physiotherapist. The research assistant will be responsible for the initial telephone screening, recruiting, and performing pre- and post-intervention assessments; this individual will be blinded to group allocation. The physiotherapist will assist with assessments and administer the interventions. Participants will initially complete a test session to confirm eligibility for the study and to obtain baseline measures, including an assessment of reactive balance control. Upon completion of the initial assessment, information required for group allocation and information pertaining to participant eligibility will be communicated by the research assistant to the principal investigator. Upon randomization, the principal investigator will communicate group allocation to the physiotherapist. At the post-training, interim follow-up, and final follow-up assessments, the research assistant will be asked to guess the group allocation for each participant. The research assistant will also be asked to rate how confident they are in their guess of group allocation, and if they have received any information from the participant or other research personnel to violate blinding. If the research assistants’ guesses of group allocation are significantly greater than 50 % correct another researcher not involved with data collection or training will review the video-taped assessments and re-score the tests.

### Trial interventions

Interventions will be administered on a 1:1 basis (i.e., one physiotherapist per participant) by a trained and licensed physiotherapist. Interventions will follow a general guide but will be tailored to the individual participants’ ability, and individualized instructions and task modifications will be used to target participant-specific impairments in balance control. Participants will complete two 1 h training sessions per week for 6 weeks. Additionally, participants will be asked to return for two 1 h ‘booster’ training sessions 3 and 9 months following the initial training period. These booster sessions may help participants to retain some of the benefits of training [40, 41]. The proposed amount of training is similar to previous studies of perturbation training [32, 34, 42, 43]. To help to alleviate barriers to attending the program we will compensate participants for their travel expenses.

#### Group 1: ‘traditional’ balance training (control group)

The control group will complete a ‘traditional’ balance training program that focuses on maintaining stability during voluntary movement, rather than responding to instability. As previous research found no effect of such ‘traditional’ balance training on fall rates post-stroke [29, 30], we expect that the control participants will not be at a reduced risk of falling as a result of completing this program. Participants assigned to the control group will complete the Keep Moving with Stroke program [44]. This is an exercise program for individuals living in the community following stroke developed by a group of physiotherapists, and is based on balance and mobility interventions evaluated in clinical trials [45–48]. While the Keep Moving with Stroke program was initially designed to be delivered in a group format, it will be delivered 1:1 in the current study to match the attention received by the physiotherapist in the perturbation training program. Each session includes a 5−10 min warm-up followed by 40 min of mobility and balance-related exercises, and a 5−10 min cool-down with stretching. Full details of this program can be found online [44].

#### Group 2: perturbation training

The perturbation training program is grounded in motor learning principles of practice variability, practice order, feedback, guidance, instruction, and focus of attention, and in exercise physiology principles of overload, adaptation, progression, individualization, and specificity [31]. The initial assessment of reactive balance control will be used to identify participant-specific impairments in the control of reactive stepping; these impairments will then be targeted in the training program. A variety of tasks will be included to induce external or internal postural perturbations. External perturbations will be caused by forces outside the participants’ control (e.g., a push or pull from the physiotherapist). Internal perturbations are caused when the participant fails to control the centre of mass-base of support relationship during voluntary movement; ‘agility’ tasks, such as kicking a soccer ball, can be used to induce internal perturbations. Each session will include a 5−10 min warm-up, voluntary tasks that may induce internal perturbations, voluntary tasks combined with up to 60 external perturbations, and a 5−10 min cool-down. The number of repetitions is similar to previous studies [31, 32, 42], and our pilot testing indicates that individuals with sub-acute stroke can tolerate up to 30 perturbations in a 20 min session [22]. The task difficulty will be set such that participants will require an upper extremity response or external assistance (i.e., from the overhead harness or physiotherapist) or take more than 2 steps to regain stability approximately 50 % of the time. The progression in voluntary tasks occurs on a continuum from stable to mobile, and from predictable to unpredictable [49]. Additionally, progression occurs by increasing the magnitude of the external perturbation, or imposing sensory or environmental challenges. Examples of some of the training tasks are included in Table 1; a detailed training manual is available from the authors.

**Table 1 Tab1:** Examples of voluntary tasks used in the perturbation training program

Week	Task type	Definition	Examples
1	Stable	Participants do not move their feet.	• Standing with eyes closed.
			• Shifting weight left/right or forward/back.
2-3	Quasi-mobile	Participants move their feet but remain ‘on the spot’.	• Rapid stepping forward and back.
			• ‘Walking’ in place.
4−5	Mobile	Participants move around the room.	• Walking forward or backward.
			• Side stepping.
6	Mobile & unpredictable	Participants move around the room in ways they cannot predict.	• Kicking a soccer ball against a wall.
			• Walking with sudden stops and changes in direction.

Tasks are completed alone and with external postural perturbations. External perturbation methods include ‘lean and release’ perturbations where participants lean forward, backward, left or right on the physiotherapists hands and are released suddenly (during stable tasks); a push or pull from the physiotherapist; or a trip with the physiotherapists foot (during mobile tasks). Each task can be modified to increase or reduce the difficulty, depending on participants’ abilities

#### Safety during training sessions

The physiotherapist will document activities in each session and deviations from recommended activities (e.g., due to participant fatigue). Participants will be asked to rate their perceived level of challenge (using a 5-point scale) at 10 min intervals throughout the sessions.

Blood pressure and heart rate will be measured and documented prior to the start of each session, and may be re-measured periodically throughout the session at the discretion of the physiotherapist. The session may be terminated if resting blood pressure or heart rate is outside of an acceptable range (systolic blood pressure: 90−140 mmHg; diastolic blood pressure: 60−90 mmHg; heart rate: 60−100 beats per minute). The decision to continue or terminate the study visit will be made by the physiotherapist, considering factors such as the participants’ usual resting blood pressure and heart rate, how far the measured values are outside of the acceptable range, the participants’ usual medications (e.g., beta-blockers), and the participants’ perception of how they are feeling. If the visit is terminated, the physiotherapist may advise that the participant follow-up with his/her primary care physician or may consult with on-site physicians.

Participants will be asked to bring their usual orthosis/brace, mobility aids, eyeglasses, and any medications taken on a *pro re nata* basis to training sessions. Participants will be deemed to have poor foot or ankle sensation and/or motor control if they meet any of the following criteria: Chedoke-McMaster Stroke Assessment (CMSA [50]) foot stage 3 or lower; unable to detect light touch with a cotton ball on fewer than 4 out of 5 trials; or unable to identify that that ankle has been placed into dorsiflexion, plantarflexion, inversion or eversion by the examiner on fewer than 8 out of 10 trials. Participants assigned to both groups with poor foot or ankle sensation and/or motor control who do not usually wear an ankle-foot orthosis will be required to wear an Aircast ankle brace for the training sessions to prevent ankle injury.

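### Both sensory criteria of the ankle-brace rule are worded backwards: intact sensation is flagged as poor, and only the worst scorers on both tests can escape the brace

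*Protocol article*

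**What the plan says.** The rule is in the protocol article under Safety during training sessions. It is introduced by "Participants will be deemed to have poor foot or ankle sensation and/or motor control if they meet any of the following criteria". Three criteria follow:

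- Motor: a CMSA score of "foot stage 3 or lower".
- Light touch: "unable to detect light touch with a cotton ball on fewer than 4 out of 5 trials".
- Ankle position: "unable to identify that that ankle has been placed into dorsiflexion, plantarflexion, inversion or eversion by the examiner on fewer than 8" of 10 trials.

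The consequence applies to both groups. Flagged participants who "do not usually wear an ankle-foot orthosis will be required to wear an Aircast ankle brace for the training sessions to prevent ankle injury". No other section restates or corrects these cut-offs.

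**The concern.** The two sensory criteria contain a double negative. *Unable* counts failures and *fewer than* asks for few of them, so each criterion is met by people who do well on the test. This contradicts three things in the same section: the label being defined (poor sensation), the motor criterion beside it (where a low stage correctly counts as poor), and the stated aim of preventing ankle injury.

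The wording matters because the rule is mandatory. The blood-pressure and heart-rate limits in the same section leave the decision to the physiotherapist; the brace rule does not. It applies in both arms, and the perturbation arm is demanding: up to 60 external perturbations per session, with difficulty set so that about half the time participants need an arm response, outside help or more than 2 steps (Group 2: perturbation training). Perturbations in mobile tasks include trips by the physiotherapist's foot (note to Table 1). Followed literally, the rule braces people who do not need it and leaves unbraced the few with the worst results on both sensory tests.

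**Working it through.** There is no stated figure to reproduce; the check is of a decision rule.

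**Inputs**, all from Safety during training sessions: 5 touch trials with a cut-off of 4; 10 position trials with a cut-off of 8; any one criterion suffices. Take a participant with CMSA foot stage 4 or higher (motor criterion not met) and no usual orthosis. Let *d* be touches detected (0–5) and *c* positions identified (0–10). Failures are then 5 − *d* and 10 − *c*.

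**The two rules**

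- As printed: flag if (5 − *d*) < 4 or (10 − *c*) < 8, that is, *d* ≥ 2 or *c* ≥ 3.
- With *able* in place of *unable*: flag if *d* < 4 or *c* < 8.

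| | As printed | Corrected |
|---|---|---|
| Touch scores flagged | 2–5 of 5 | 0–3 of 5 |
| Position scores flagged | 3–10 of 10 | 0–7 of 10 |
| Exempt overall | touch 0–1 and position 0–2 | touch 4–5 and position 8–10 |

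Of the 6 × 11 = 66 possible score pairs, each rule exempts 2 × 3 = 6. The exempt sets do not overlap, so the rules disagree on 6 + 6 = 12 pairs and agree on 66 − 12 = 54. The 6 best pairs are wrongly flagged and the 6 worst wrongly exempted. These are unweighted counts of score pairs, not shares of participants.

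**The other possible parse.** If the phrase means *unable to achieve a result of fewer than 4 detections*, it flags those who detect 4–5 of 5. Intact sensation is flagged on this reading too.

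**Two limiting cases** (same participant profile)

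1. Intact sensation, *d* = 5 and *c* = 10. As printed: 0 failures < 4, so braced. Corrected: 5 ≥ 4 and 10 ≥ 8, so not braced.
2. No touch sensation, *d* = 0, and pure guessing on position. As printed, touch gives 5 failures, which is not fewer than 4, so the participant is exempt if at most 2 positions are guessed correctly. With *c* ~ Binomial(10, *g*), where *g* is an assumed chance of a correct guess:
   - *g* = 0: P(*c* ≤ 2) = 1.00.
   - *g* = 0.25 (four equally likely directions): 0.75¹⁰ + 10 × 0.25 × 0.75⁹ + 45 × 0.25² × 0.75⁸ = 0.056 + 0.188 + 0.282 = 0.526.
   - *g* = 0.5: (1 + 10 + 45)/1024 = 0.055.

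   Under the corrected rule this participant is always braced, because 0 < 4.

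**The case against.** The strongest reply is that this is a copy-editing slip whose meaning nobody would miss. The sentence says it is defining poor sensation, and sessions are given "by a trained and licensed physiotherapist", who is unlikely to brace someone because their sensation is intact. That stands, and it is why the point is minor.

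Other objections bear on its weight:

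- The printed rule is not the exact opposite of the intended one. Touch scores of 2–3 and position scores of 3–7 are flagged by both. This is correct: the direction is reversed, but the errors fall only on the best scorers and on the worst scorers on both tests.
- The harmful direction needs an unusual participant: very poor on both sensory tests, CMSA foot stage 4 or higher, no usual orthosis, and still able to stand unsupported for more than 30 s and tolerate at least 10 perturbations (Participants). Nothing in the article shows that such a person would enrol. The guessing calculation shows what the rule would do with one; its range of 0.05 to 1.00 is too wide to serve as an estimate.
- The working documents are not shown. The article notes that "a detailed training manual is available from the authors", but this refers to the perturbation programme, and nothing says that it contains the brace rule. The slip may never have reached practice.
- Trial validity is unaffected, since the rule is the same in both groups.

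None of this makes the printed rule right. The article states specific cut-offs, so this is not a detail left to a fuller document, and applying them as written gives the wrong decision.

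**Conclusion.** The concern holds: both sensory criteria are wrong as written. Read literally, they require a brace for participants with perfect sensory scores and, given CMSA foot stage 4 or higher and no usual orthosis, exempt only those with 0–1 of 5 touches and 0–2 of 10 positions. That conclusion needs no assumption beyond the text, and both ways of parsing the phrase flag intact sensation. Only the exemption probability for a participant without touch sensation (0.53, range 0.05 to 1.00) rests on an assumed guessing rate.

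It is a minor correction to a safety rule. The number of participants affected cannot be estimated from the article, and the practical effect is probably small. The primary outcome, sample size and analysis are untouched, and no between-group bias is shown.

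**What to change.** Replace *unable* with *able* in both sensory criteria, so that a participant is flagged if light touch is detected on fewer than 4 of 5 trials, or ankle position is correctly identified on fewer than 8 of 10 trials. This is the smallest edit that keeps both printed numbers and fits the label; the investigators should confirm that these are the cut-offs they meant. Then check that the training manual and the assessment forms state the rule in the same direction. The cost is two words in one sentence and a short document check.

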### Outcome measures

Participants will be followed for 12 months following completion of the initial training period. During this time, falls, activity, and participation will be reported regularly. Balance confidence and functional balance and mobility will be assessed at study enrolment, immediately after the initial training period, six-months after the initial training period, and at the end of the 12 months follow-up. All data will be collected by a trained research assistant who is blinded to group allocation. Table 2 summarizes that measures that will be taken at each time point.

**Table 2 Tab2:** Summary of outcome measures and assessment time points

	Pre-training assessment	Post-training, interim and follow-up assessments	12-months follow-up period
Demographic and stroke information	✓		
Medical conditions	✓	✓	
Medications	✓	✓	
NIH-SS	✓		
CMSA	✓		
Lean-and-release test	✓		
BBS	✓	✓	
Mini-BES	✓	✓	
TUG	✓	✓	
ABC	✓	✓	
Falls reporting^a^	✓		✓
PASIPD^b^	✓		✓
SIPSO^b^	✓		✓

^a^Reported continuously throughout the 12-months follow-up period

^b^Questionnaires completed approximately every 2-months throughout the 12-months follow-up period

#### Cohort descriptors

The following demographic and medical information will be recorded at the time of study enrolment in order to characterize the study cohort: age, sex, height, weight, time since stroke, lesion location, other medical conditions, prescription medications, the National Institutes of Health Stroke Scale (NIH-SS [51]), and CMSA foot and leg scores [50]. Information regarding past medical history will be obtained by self-report and, when possible, will be verified from the participants’ hospital charts. The NIH-SS is an 11-item scale that provides a gross measure of the effects and severity of stroke. The NIH-SS has shown good intra- (ICCs = 0.93) and inter-rater (ICCs = 0.95) reliability [52]. The CMSA assigns a score according to the level of motor recovery in the foot and leg, and is frequently used to evaluate motor impairment post-stroke in clinical settings. The CMSA foot and leg scores have good intra- (ICCs = 0.94-0.98) and inter-rater (ICCs = 0.85-0.96) reliability [50].

#### Primary outcome – falls

A fall is defined as “an event that results in a person coming to rest unintentionally on the ground or other lower level” [14]. Participants will complete a 12-month falls monitoring period after the initial 6-week training period. Participants will be provided stamped addressed postcards containing a calendar to record falls, which they will complete daily. Participants will be asked to return each postcard to the research team fortnightly. Participants will receive a monthly study newsletter by mail containing health-related articles of interest, as well as a reminder to complete the postcards. If a participant does not return a postcard within two weeks, the research assistant will call them. In this telephone call, the research assistant will try to ascertain if the participant has experienced a fall in the previous two weeks. This method is considered the ‘gold standard’ for falls reporting [53]. Participants who report a fall on the calendar will be contacted by the research assistant to complete a short questionnaire in order to determine the cause and consequences of the fall.

#### Secondary outcomes (follow-up) – activity and participation

Fall rates may increase with increasing physical activity and mobility [54–60]. It is likely that when an individual with reduced balance control attempts to mobilize, s/he is at increased risk of losing balance and falling [61, 62]. Therefore, it is important to determine if fall rates are influenced by physical activity [63]. Conversely, improved balance control and reduced fear of falling should increase participation in activities. Physical activity and participation will be evaluated with the Physical Activity Scale for Individuals with Physical Disabilities (PASIPD [64]) and the Subjective Index of Physical and Social Outcome (SIPSO [65]), respectively, at six time points (every two months) during the 12-month follow-up. Regular administration of the questionnaires will provide an estimate of physical activity and participation over the duration of the follow-up period. The PASIPD is a 13-item questionnaire in which participants are asked to indicate the frequency and duration of recreational, household, and occupational physical activities completed in the previous 7 days. The PASID has been validated within a group of individuals with various physical disabilities, including those with stroke, showing good test-retest reliability (ρ = 0.77) and criterion validity when compared to accelerometer-based activity monitoring (ρ = 0.30; [66]). The SIPSO is a 10-item questionnaire that evaluates physical and social integration and participation in ‘normal’ daily life [65]. The SIPSO has good internal consistency (Cronbach’s α = 0.92) and test-retest reliability (ICC = 0.91) among those with stroke [65].

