Despite control challenges associated with executing reactive steps, individuals with impaired balance control are increasingly dependent on these stepping responses because they are the last option to prevent falling. Because stroke survivors are at a high risk of falls, it is essential to develop approaches to re-train compensatory stepping after stroke. There is compelling evidence that physical exercise prevents falls among older adults [28]; however, no exercise intervention has effectively reduced risk of falls among individuals with stroke [29, 30]. More specific exercise, that is, perturbation training involving repeated exposure to applied balance disturbances, is necessary to achieve improvements in the control of fast reactive movements [22, 31–34]. Perturbation training is an emerging and promising treatment strategy for preventing falls [35]. The novelty of perturbation training is in the focus on speed of processing and execution of limb movements, as well as rapid restabilization; this differs from ‘traditional’ balance training programs using voluntary movements that allow participants to control speed. Such training is specific to the demands of balance recovery reactions to prevent a fall following a ‘real life’ loss of balance.

The primary objective of this study is to determine if a novel perturbation-based training program focused on improving reactive stepping in individuals with chronic stroke will reduce the risk for falls in the community. Secondary objectives are to determine the effect of perturbation training on balance confidence and activity restriction, and functional balance and mobility. Our primary hypothesis is that individuals with chronic stroke who complete perturbation training will be less likely to experience a fall up to 12-months following completion of the program, compared to individuals who complete a ‘traditional’ balance training program (control group). Our secondary hypothesis is that, compared to individuals in the control group, individuals with stroke who complete the perturbation training program will show: increased balance confidence; increased participation in daily activities in the year following completion of the program; and greater gains in functional balance and mobility.

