
### Statistical analysis and sample size

Negative binomial regression will be used to compare fall rates between the two groups and logistic regression will be used to compare the proportion of fallers between the two groups. If the groups differ on prognostic factors (e.g., stroke severity) or on physical activity during the follow-up period (i.e., PASIPD scores) then multiple negative binomial/logistic regression will be used. Intent-to-treat analysis will be used; all individuals with some falls-monitoring data will be included in the analysis. Survival analysis may be considered if a large number of individuals do not complete the entire 12-month follow-up. Exploratory per-protocol analysis and/or comparison of fall rates between those who return for the ‘booster’ training sessions and those who do not may also be conducted. Repeated-measures analysis of variance, with group-by-time interaction, will be used to evaluate the effect of the interventions on secondary outcome measures (e.g., functional balance measures, balance confidence). The interaction effect will reveal if there is a greater pre- to post-training improvement in the perturbation training group compared to the control group.

The target sample size has been estimated using a formula for negative binomial regression described elsewhere [78]. Assuming a rate of falls in the control group of 1.75 per person per year [27], a reduction in rate of falling of 46 % in the perturbation training group [35], mean follow-up time of 11 months per person (i.e., some participants will be lost to follow-up before 12 months), level of significance (α) of 0.05, and power (1-β) of 0.8, we estimate that 37 participants per group will be required to show significant effects. From previous studies [32, 79], we expect that ~20 % of individuals will withdraw prior to completing the intervention. While many of these individuals will be willing to complete the 12-month falls monitoring period and could be included in intent-to-treat analysis, we conservatively assume that 20 % of individuals will withdraw from the study. Therefore, we will aim to recruit at least 46 participants per group (i.e., 92 participants total).

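### The pre-to-post interaction named for secondary outcomes does not fit the activity and participation questionnaires (PASIPD, SIPSO), and the text leaves out the baseline score that Table 2 lists for them

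*Protocol article*

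**What the plan says.** **Hypothesis.** In the Background, one secondary hypothesis is that perturbation training leads to "increased participation in daily activities in the year following completion of the program".

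**Schedule in the text.** The section on follow-up secondary outcomes has PASIPD (activity) and SIPSO (participation) completed "at six time points (every two months) during the 12-month follow-up". Under Outcome measures, enrolment and post-training assessments are named for other outcomes: "Balance confidence and functional balance and mobility will be assessed at study enrolment, immediately after the initial training period".

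**Schedule in Table 2.** Both questionnaires are ticked at the pre-training assessment and in the 12-month follow-up period. They are blank in the column for the post-training, interim and follow-up assessments. Footnote b reads "Questionnaires completed approximately every 2-months throughout the 12-months follow-up period" and does not remove the pre-training tick.

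**Analysis.** Under Statistical analysis and sample size, "Repeated-measures analysis of variance, with group-by-time interaction, will be used to evaluate the effect of the interventions on secondary outcome measures", with examples in brackets ("e.g., functional balance measures, balance confidence"). The next sentence gives the interpretation: "The interaction effect will reveal if there is a greater pre- to post-training improvement in the perturbation training group compared to the control group". PASIPD appears once more in that section, where a group difference "or on physical activity during the follow-up period (i.e., PASIPD scores") would prompt covariate adjustment of the falls models.

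**The concern.** The hypothesis concerns how much people participate during the year after training. The stated test concerns improvement from before to immediately after training. PASIPD and SIPSO have no immediate post-training score on either schedule, so the stated interpretation cannot be applied to them as written. The other mention of PASIPD decides on covariates for the falls analysis and does not test this hypothesis. SIPSO is the only instrument that the article assigns to participation.

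Two things are at stake. First, an inefficient contrast raises the chance that a real, sustained benefit is missed and then reported as no effect on participation. Second, a site working from the text alone could omit the pre-training questionnaires, and a baseline cannot be recovered once training has begun.

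**Working it through.** The article gives no figure for this comparison, so there is none to reproduce. The check compares the power of the stated contrast with that of one matched to the hypothesis.

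**Inputs from the protocol article**
- n = 37 per group and alpha = 0.05 (Statistical analysis and sample size). Two-sided testing is assumed, as sidedness is not stated.
- Test-retest values of 0.77 for PASIPD and 0.91 for SIPSO (section on activity and participation).
- Six follow-up scores (text), plus one pre-training score (Table 2).

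**Assumptions**
- A steady group difference d of 0.3 or 0.5 SD at all six follow-ups and none at baseline.
- Equal correlation rho between any two occasions, and no missing scores.
- rho = 0.5 and 0.7 are added because test-retest values probably overstate correlation over gaps of two months to a year.

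**A. Interaction with the Table 2 baseline (seven occasions)**

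The group difference is 0 at baseline and d at the other six. Its squared deviations from its own mean sum to (6/7)d². The noncentrality is (n/2)(6/7)d²/(1 − rho), on 6 and 72 × 6 = 432 degrees of freedom.

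Example, d = 0.3 and rho = 0.7: 18.5 × 0.857 × 0.09 / 0.3 = 4.76, power 32%.

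**B. Mean of the six follow-ups, adjusted for baseline**

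The mean of six has variance rho + (1 − rho)/6. Its covariance with baseline is rho, so the residual variance is v = rho + (1 − rho)/6 − rho². The noncentrality is (n/2)d²/v, on 1 and 71 degrees of freedom.

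Example, d = 0.3 and rho = 0.7: v = 0.70 + 0.05 − 0.49 = 0.26; 18.5 × 0.09 / 0.26 = 6.40, power 70%.

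| rho | v | A, d = 0.3 | B, d = 0.3 | A, d = 0.5 | B, d = 0.5 |
|---|---|---|---|---|---|
| 0.5 | 0.333 | 19% | 60% | 52% | 96% |
| 0.7 | 0.260 | 32% | 70% | 78% | 99% |
| 0.77 | 0.215 | 41% | 78% | 89% | >99% |
| 0.91 | 0.097 | 86% | 98% | >99% | >99% |

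**Where the loss arises.** Put the noncentrality of 4.76 from the example in A on a single contrast, mean follow-up minus baseline, with 1 and 72 degrees of freedom. Power rises from 32% to 58%. Spreading the effect over 6 degrees of freedom therefore accounts for most of the gap. Using baseline as a covariate rather than subtracting it brings the rest, to 70%.

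**C. Interaction with the six follow-up scores only**

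A constant difference has no deviation from its own mean, so the noncentrality is 0 and power equals alpha, 5%, for any d and rho. This case applies only if no baseline is taken.

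**The case against.** The strongest reply is that the baseline is already planned. Table 2 ticks it, and the text omits it without excluding it. The section concerned is headed as follow-up outcomes, so it naturally describes follow-up administration. Falls reporting follows the same pattern: ticked at pre-training in the table, but described in prose only for follow-up. This stands. Text and table need reconciling, but they do not flatly contradict each other.

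A reader might infer that the stated test cannot answer the participation hypothesis at all, or that its power is 5%. The documents do not support that. On the Table 2 schedule a benefit that appears after baseline and persists is a group-by-time interaction. At the printed SIPSO reliability of 0.91 the test has 86% power even for 0.3 SD. The 5% figure belongs only to a trial that skips the baseline. Nor is the missing post-training visit a design fault, since the hypothesis concerns the year afterwards and six scores in that year suit it.

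It can also be said that the bracketed examples are exactly the pre-post outcomes, that repeated-measures ANOVA yields a group main effect too, and that choosing a contrast is commonly left to an analysis plan, which is not shown. This stands in part. The examples do not exclude PASIPD and SIPSO, however, and the article does not leave the contrast open: it names one and says how to read it. The main effect over six unadjusted follow-ups is not named as the test. For d = 0.5 it would have power of about 79%, 66% and 60% at rho = 0.5, 0.77 and 0.91, below the baseline-adjusted mean throughout.

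**Conclusion.** The point holds as a mismatch between contrast and hypothesis, together with a baseline that the text should name. The stated interpretation does not apply to PASIPD or SIPSO, and the interaction is an inefficient test of a sustained difference.

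The size depends on the correlation between occasions. For a steady 0.3 SD difference, the baseline-adjusted mean gains roughly 37 to 41 percentage points of power at correlations of 0.5 to 0.77, and 12 points at 0.91. For 0.5 SD the gain is 44 points at 0.5 and 21 at 0.7, and it is negligible at 0.91. These figures assume 37 analysed per group, equal correlation, complete scores and an effect that is constant over the year. Neither the effect sizes nor the correlations of 0.5 and 0.7 come from the article. An effect that grows or fades would change the comparison.

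The change should be made because it costs little and bears on a stated hypothesis. The primary falls analysis is not affected.

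**What to change.** 1. Under Outcome measures and in the section on activity and participation, state that PASIPD and SIPSO are also completed at the pre-training assessment, as Table 2 shows.
2. Under Statistical analysis and sample size, limit the pre- to post-training interaction to the balance, mobility and balance-confidence measures.
3. For PASIPD and SIPSO, compare the groups on the average of the six follow-up scores, adjusted for the pre-training score. A mixed model over the six follow-ups, with baseline as covariate and the group difference averaged over time as the test, does this.

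The cost is a few sentences of protocol wording and one different model for two secondary outcomes. No visit or questionnaire is added, because Table 2 already lists the baseline. The wording should be settled before sites enrol from the text alone, since a missed baseline cannot be collected later.
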